### Study design

A two-arm RCT with an intervention condition (mental health and suicide gatekeeper resource) and a waitlist control condition will be conducted. Outcome measures will be administered on three occasions: preintervention, postintervention (4 weeks after receiving access to the intervention) and 12-week follow-up.

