### Procedure

After randomisation, all participants will be informed of their trial condition via the email address they provided in the preintervention survey. At this time, participants allocated to the intervention condition will be provided with instructions and login details to access the mental health and suicide gatekeeper resource via an online learning platform. Participants will be provided with access to the resource over a 4-week period and encouraged to work through it in several sittings. For intervention-condition participants who have not completed the resource, weekly email reminders to access the resource will be sent.

During the intervention phase, the trial participants in the waitlist control condition will continue their usual activities. After the 4-week intervention period, all participants will be invited to complete an online postintervention self-report survey. Participants will be invited to complete a third and final online self-report survey at 12 weeks postintervention. Participants will receive notification of the postintervention and follow-up surveys via email and will receive up to two email reminders if the surveys are not completed. Surveys will take approximately 20–30 min to complete. To assist with participant retention in the trial, all participants will be offered a AU$15 egift card for completing the postintervention and follow-up surveys, which will be sent to participants via the email details provided during registration. Upon completion of the trial period, participants in the waitlist control condition will be provided access to the mental health and suicide gatekeeper resource and will have access to it for 4 weeks.

A subset of participants who were allocated to the intervention condition will also be invited to participate in a qualitative interview. Participants will have the opportunity to indicate their interest in undertaking an interview at the end of the follow-up survey. The online interview will take up to 60 min to complete and will consist of a number of open-ended questions to stimulate discussion on parent views of the resource, guide future refinement of the resource and identify optimal dissemination pathways. Participants will be offered a AU$40 egift card to compensate them for their time. The flow of participants within the trial is presented in figure 1.

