#### Resource satisfaction, acceptability and engagement

Among intervention condition participants, the level of engagement with the resources will be assessed at postintervention using resource backend data (eg, logins and completion), as well as self-report data on the number of times the resource was accessed, time spent on the resource, if participants downloaded any information sheets and whether they shared the resource content with anyone. At follow-up, participants will be asked if they accessed the resource over the previous 12-week period and, if so, which sections and, why.

Satisfaction and acceptability of the mental health and suicide gatekeeper resource will also be assessed at postintervention using a satisfaction measure adapted from a previous study.^34^ Open-ended questions at postintervention will also be used to identify what participants liked most and least about the resource, what they found to be most useful and important, the likelihood of recommending the resource to other parents and possible resource changes or additions. A list of seven potential barriers to accessing the resource will also be presented to participants, who will be asked to select any relevant barriers, with a free-text response available to nominate other barriers.^35^

Semistructured interviews of approximately 60 min will also be conducted with 15–20 intervention-condition participants to further explore motivations to use the resource, what parts of the resource were most and least helpful, if they had shared their learning with anyone and possible resource refinements and dissemination pathways. We believe this number will be sufficient to explore the perspectives of parents with a range of mental health experiences.

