#### Intervention effects

Statistical analysis of continuous measures will be undertaken on an intent-to-treat basis, including all participants randomised regardless of intervention completion or withdrawal from the study. Mixed-model repeated measures analysis of variance will be used, with measurement occasion as a within-groups factor and condition as a between-groups factor. This approach yields unbiased estimates of intervention effects under the assumption that data is missing completely at random or at random and will allow the inclusion of participants with missing data without using biased techniques, such as the last observation carried forward.^36^ For any dichotomous outcomes, a comparable binary mixed modelling approach^37^ will be used. Cohen’s d effect sizes will be calculated for each time point. If efficacy is demonstrated, exploration of potential mediators and moderators of response, such as child’s age, child’s mental health, participant gender and intervention completion, will be explored separately using three-way interaction terms and stratified models.

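### Intervention completion is listed for three-way interactions and stratified models, but it exists only in the intervention arm, so the interaction cannot be estimated and a completer stratum has no randomised comparator

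*Protocol article*

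**What the plan says.** The protocol article, under Intervention effects, describes a mixed-model repeated measures analysis "with measurement occasion as a within-groups factor and condition as a between-groups factor". It then adds an exploratory step: "If efficacy is demonstrated, exploration of potential mediators and moderators of response" is to follow. Four examples are given: child's age, child's mental health, gender and completion. All four receive one method: "participant gender and intervention completion, will be explored separately using three-way interaction terms and stratified models". Since the base model already has occasion and condition as factors, the third factor in each interaction is the listed variable.

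Two other sections fix what completion can be. Under Procedure, during the intervention phase "the trial participants in the waitlist control condition will continue their usual activities", and "Upon completion of the trial period, participants in the waitlist control condition will be provided access to the mental health and suicide gatekeeper resource". Under Resource satisfaction, acceptability and engagement, "Among intervention condition participants, the level of engagement with the resources will be assessed at postintervention using resource backend data", with logins and completion as the examples. Under Study design, "Outcome measures will be administered on three occasions: preintervention, postintervention" and a 12-week follow-up. All three occasions fall before the waitlist arm receives the resource.

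**The concern.** Child's age, child's mental health and gender can each be defined in both arms, so their interaction with condition over time has a meaning. Completion cannot: it is a behaviour after randomisation that only one arm can show. A three-way term asks whether the difference between arms varies with completion, which needs completers and non-completers in each arm. The stratified version has the same gap, because the completer stratum holds intervention participants only.

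The practical risk lies in what an analyst does when the model fails. Software may drop the aliased terms and still report an occasion × completion term, which is easily read as moderation although it only compares completers with non-completers inside one arm. Alternatively, the analyst may compare completers with the whole waitlist arm. Either way, differences between parents who finish and parents who do not may be credited to the resource.

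**Working it through.** **Scale of the planned effect.** From Sample size and power calculations: d = 0.4 for change, power 0.9, two-sided α = 0.05, pre-post correlation 0.5, target 190 per condition.

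- SD of change in units of the outcome SD: √(2 × (1 − 0.5)) = 1.
- n per arm: 2 × (1.960 + 1.282)² / 0.4² ≈ 131.3, so 132.
- With 30% attrition: 132 / 0.70 = 188.6, so 189, which agrees with the stated 190.

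The present point does not depend on this figure. It shows that the planned 0.4 is a difference in change, so any bias should be expressed on that scale.

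**Estimability.** Let C = condition (1 = intervention), K = completion (1 = completer), and T1, T2 = indicators for the second and third occasions. The saturated fixed-effect model has these columns:

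| Term | Columns |
|---|---|
| Intercept | 1 |
| Occasion | 2 |
| C | 1 |
| K | 1 |
| C × K | 1 |
| C × occasion | 2 |
| K × occasion | 2 |
| C × K × occasion | 2 |
| Total | 12 |

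Of the 2 × 2 × 3 = 12 cells, the 3 for control completers cannot occur, which leaves 9. K = 1 implies C = 1, so in every row C × K equals K, C × K × T1 equals K × T1, and C × K × T2 equals K × T2. Three columns are duplicates, and the rank is 12 − 3 = 9; a numerical rank check gave the same. The three lost terms are the ones the moderator question needs.

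If completion is instead left missing for controls, they drop out of the model, C is constant, and no interaction with condition can be estimated.

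**Size of the selection bias, for illustration.** The protocol gives no completion rate and no link between completion and change. Assume that a standard normal propensity to complete correlates ρ with change, and that the top proportion p complete. With a true effect of zero and with z the cut-off:

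- completers against all controls: d = ρ × φ(z) / p
- non-completers against all controls: d = −ρ × φ(z) / (1 − p)

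φ(z) is 0.348 at p = 0.3 or 0.7, and 0.399 at p = 0.5.

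| ρ | p | Completers | Non-completers |
|---|---|---|---|
| 0 | any | 0 | 0 |
| 0.1 | 0.3 | 0.12 | −0.05 |
| 0.1 | 0.5 | 0.08 | −0.08 |
| 0.1 | 0.7 | 0.05 | −0.12 |
| 0.2 | 0.5 | 0.16 | −0.16 |
| 0.3 | 0.3 | 0.35 | −0.15 |
| 0.3 | 0.5 | 0.24 | −0.24 |
| 0.3 | 0.7 | 0.15 | −0.35 |

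A simulation with 190 per arm agreed to within about 0.01. Adding a true effect of 0.4 that is the same for everyone shifts each entry by 0.4: completers show about 0.45 to 0.75 and non-completers about 0.05 to 0.35. That would look like moderation where there is none.

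**The case against.** The strongest reply is that little hangs on this. The step is exploratory, depends on efficacy having been shown, and completion is one example among four. The main analysis includes everyone randomised whether or not they completed, so the primary result, the sample size and the secondary comparisons are untouched. All of that stands and sets the severity.

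A second reply is that the article does not spell out the stratified contrast. That is so: completers against all controls is an inference. It is the natural one, because the completer stratum has no controls of its own, and the absence of controls follows from the text whichever contrast is chosen.

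A third is that completion may have been meant as a mediator, since the sentence covers mediators and moderators together. This does not rescue the method: only interactions and stratification are named, and they address effect modification. As the other examples are all moderators, the wording may simply be compressed.

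Three stronger readings are tempting but not supported.

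- A reader might infer that the whole moderator analysis fails. It does not; the other three variables can be defined in both arms.
- A reader might infer a larger bias by correlating completion with the level of the untreated outcome. The model includes the preintervention occasion, so a motivation difference that is equally present before and after cancels from the contrast in change. Only correlation with change biases it.
- A reader might infer that decisions on revising or disseminating the resource rest on this analysis. The protocol assigns refinement and dissemination pathways to the interviews and asks about resource changes in open-ended questions. Its statement about revision and dissemination concerns the study as a whole.

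**Conclusion.** The point holds in narrow form. That condition × completion and occasion × condition × completion cannot be estimated follows from the protocol's own text and needs no assumption. That a completer stratum lacks a randomised comparator follows equally. The size of the resulting bias is illustrative: about 0.05 to 0.35 in completers under zero effect, and the same range with opposite sign in non-completers, resting on an assumed correlation of 0.1 to 0.3 with change and assumed completion of 30% to 70%. It is zero if the correlation is zero. The error is minor and confined to one variable in an exploratory analysis. It is worth correcting because a stated method for a named variable cannot run as written.

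**What to change.** Remove intervention completion from the list for interaction terms and stratified models, and keep those methods for baseline variables defined in both arms. Examine completion only as a dose-response analysis within the intervention arm, labelled observational.

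Optionally, add a complier-average effect with randomised condition as the instrument and state the exclusion restriction. Uptake is better defined as any access than as full completion: the resource is self-paced, has three sections and offers downloadable sheets, so partial users may benefit. For example, if everyone gained 0.4 and half completed (both assumed), treating only completers as exposed would give 0.4 / 0.5 = 0.8, twice their true effect.

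Any mediator should be analysed with a mediation model using a variable measured in both arms, not with interaction terms.

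The cost is a change of wording and one small exploratory analysis, with a wider interval than the main comparison. Completion data are already to be collected.

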#### Satisfaction and acceptability

Descriptive statistics will be used to summarise resource use, resource satisfaction and acceptability. Deidentified transcribed interview data will be qualitatively analysed using framework analysis, with a focus on examining user experience, preferences for content and potential barriers to access. Framework analysis was designed to address social policy research questions^38^ and has been used frequently in health research.^39^ It follows a systematic process of inductive coding, generating a table of findings across participants that is conducive to interpretation and input from multiple researchers.

### Ethics and Dissemination

The study will establish the efficacy of the gatekeeper resource and will inform future resource revisions and dissemination pathways. The ethical aspects of the study were approved by the Australian National University Human Research Ethics Committee (Protocol 2023/195). Prior to participating, the participant information sheet will be displayed, with participants providing informed digital consent to participate. All participants included in the trial will have access to information on crisis support numbers and mental health websites for use if they are feeling distressed. This information will be included on the information sheet provided to participants, as well as at the end of each survey.

All research data will be securely stored at the Australian National University for at least five years from the date of any publication arising from the research and will be accessible to the research team. At the end of the five-year period, all electronic survey and transcription data will be archived in a deidentified format (all reasonably identifying information removed) and may be shared with other researchers, with permission from the original research team.

Results of the current study will be communicated in aggregate form to key stakeholders, parents/carers, mental health practitioners, education providers, and the academic community through community forums, academic conferences and peer-reviewed publications.

### Trial status

Recruitment for the trial commenced on 21^st^ September 2023, with recruitment aiming to be complete by the end of May 2024.
